### Outcome Measures

#### Primary Endpoints

The main objective of this study is to demonstrate that treatment with nabiximols is superior to placebo in patients with TS/CMT. The primary outcome variable will be response to treatment according to YGTSS-TTS, defined as a reduction in YGTSS-TTS of at least 30% (compared to baseline) after 9 weeks of stable treatment.

#### Secondary Endpoints

Key secondary analyses will be performed on the continuous YGTSS-TTS changes from baseline with an ANCOVA model adjusted for the baseline YGTSS-TTS and center. Further secondary outcomes are improvements on other clinical variables: YGTSS-Global Score (sum of TTS and global impairment), MRVS, CGI-I, CGI-S, ATQ, GTS-QoL, PUTS, BDI-II, Y-BOCS, CAARS, BAI, PSQI, I-8, SF-12, and RAQ. These measurements are recommended for clinical trials in TS in order to assess the full spectrum of the disease including psychiatric comorbidities and patients' quality of life. Besides the YGTSS-TTS we will use the MRVS - an observational examiner tic assessment - as well as the ATQ, which is a self-assessment scale for tics. In addition, the YGTSS Global score takes into account the overall tic-related impairment on a patient's life, similar to the CGI-I and CGI-S that measure overall clinical impairment and improvement. Finally, the GTS-QoL is used to assess disease specific quality of life. The PUTS is an instrument that measures premonitory urges often preceding the tics. To assess comorbid pathologies, we will use the BDI-II to assess depression, Y-BOCS for obsessions and compulsions, CAARS for ADHD, BAI for anxiety, PSQI for sleep disturbances, I-8 for impulsivity, RAQ for rage attacks, and SF-12 for overall health. Other secondary endpoints are the outcome variables from the study part on driving ability “Fitness to drive.”

#### Safety Assessments, Quality Assurance and Ethics

Safety assessments include (serious) (S)AEs, C-SSRS, blood pressure, and pulse at each clinic visit. With respect to subject's driving ability, neurological and psychological impairment will be evaluated by a psychologist and a research physician and documented at each clinic visit.

To assure data quality and patients' safety, regular monitoring visits will be performed and an independent data monitoring committee (DMC) will be established. The trial will be conducted following the principles of ICH-GCP, the German Drug Law (AMG), and the Declaration of Helsinki. Study protocol including possible amendments, patient information with consent and substantial amendments will be/were approved by the responsible ethics committees and the federal authorities.

### Sample Size Calculation

The sample size calculation is based on a previous trial, in which 24 patients with TS had been randomized to 6 weeks of THC or placebo medication with a ratio of 1:1 (drop-out rate 17%: THC *n* = 3, placebo *n* = 1) (8). Under the assumption that the relative reduction on YGTSS-TTS is normally distributed in each treatment group, the probabilities for a reduction of at least 30% (criteria for treatment response) were calculated as 0.010 for placebo and 0.294 for the active arm. These calculations refer to an intention-to-treat (ITT) population, where missing values for YGTSS-TTS response at the end of treatment were set to non-response. This approach was chosen due to its higher robustness in regard to small datasets, obtaining more conservative values than the observed responder rates. The sample size calculations were conducted using nQuery 7.0 software and are based on an exact Fisher-test with a two-sided significance level of 5%, a power of 90%, and the above-mentioned responder rates (placebo = 0.010, THC = 0.294). Under a randomization ratio of 2:1, the resulting group sizes were *n* = 50 for nabiximols and *n* = 25 for placebo. To compensate for a potentially diminished treatment effect due to self-medication, non-compliance, and drop-out, we decided to increase the calculated sample size by ~30%. Thus, we decided to include 64 patients in the active arm and 32 in the placebo arm, adding up to a total sample of 96 patients.

### Statistical Analysis

#### Primary Analysis

The primary analysis will be carried out in the ITT population and use the YGTSS-TTS as criterion for a binary responder variable. A patient will be considered a responder, if a >30% decrease in YGTSS-TTS is observed as compared to baseline. The primary analysis of the responder proportion will be done with a Mantel-Haenszel estimate for the risk difference (active treatment minus placebo) stratified by center. If the lower bound of the corresponding 95%-confidence interval is above 0, superiority of the active treatment over placebo as assessed by YGTSS-TTS responder criterion is demonstrated. The two-sided type-I-error rate will be set to 5%.

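### The primary superiority rule names no interval method, and with the usual Mantel-Haenszel variances it exceeds the stated type I error at common response rates of about 3% and above

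*Protocol article*

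**What the plan says.** Under Primary Analysis, the article compares responder proportions in the ITT population by a "Mantel-Haenszel estimate for the risk difference (active treatment minus placebo) stratified by center". The decision criterion is that interval alone: "If the lower bound of the corresponding 95%-confidence interval is above 0, superiority of the active treatment over placebo" is then regarded as demonstrated. The same paragraph sets the two-sided type I error at 5%, which is 2.5% in the direction of superiority. It does not say how the interval is to be computed.

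Under Sample Size Calculation, the planning rates are "placebo = 0.010, THC = 0.294". The calculations "are based on an exact Fisher-test with a two-sided significance level of 5%, a power of 90" per cent, giving 50 and 25 patients, which are then raised to 64 and 32. Randomisation is 2:1 and stratified over six centres.

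**The concern.** The interval that goes by default with a Mantel-Haenszel risk difference is the estimate plus or minus 1.96 standard errors, using a variance estimated from the observed cell counts. When the smaller arm has no responders, that arm adds little or nothing to the variance, so the lower bound sits too high. With 32 placebo patients and low response this is not a rare event: at a true rate of 5%, the chance of no placebo responder is 0.95^32 = 0.19.

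The false-positive rate of the single confirmatory test is at stake. The hierarchical fitness-to-drive test also opens only after this rejection, so a false primary claim would open it as well.

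**Working it through.** **Inputs.** From the article: 64 and 32 patients, six centres, lower 95% bound above 0, two-sided 5%, planning rates 0.294 and 0.010. Assumed: centre sizes (the article gives none) and the variance formula.

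**The plan's own figure.** Exact enumeration of Fisher's test at 0.294 against 0.010, with 2.5% in the direction of superiority, gives 89.9% power at 48/24 and 91.7% at 50/25. So 50/25 is the smallest 2:1 design reaching 90%, and the stated figure reproduces. At 64/32 the power is 98.2%.

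**One data set, unstratified: 4/64 against 0/32.**
- Risk difference: 4/64 − 0/32 = 0.0625.
- Wald variance: 0.0625 × 0.9375/64 + 0 = 0.000916; SE = 0.0303. Lower bound: 0.0625 − 1.96 × 0.0303 = +0.003. Superiority is declared.
- Variance under the null, with pooled rate 4/96 = 0.0417: 0.0417 × 0.9583 × (1/64 + 1/32) = 0.00187; SE = 0.0433. Then z = 0.0625/0.0433 = 1.44, p = 0.149.
- Fisher two-sided p = 0.298. Miettinen-Nurminen lower bound −0.048; Newcombe −0.051.

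The null variance is about twice the Wald variance (0.00187/0.000916 = 2.0). With no placebo responder, Fisher's two-sided test and both score-based intervals need 8/64 (Fisher p = 0.049).

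**The same data, stratified.** Take four centres of 11:5 and two of 10:6, with one active responder in each 11:5 centre. Let n1, n0 and N be a centre's active, placebo and total numbers.
- Sum of weights n1·n0/N: 4 × 55/16 + 2 × 60/16 = 21.25. Risk difference: (4 × 5/16)/21.25 = 0.0588.
- Greenland-Robins: with no placebo responders, each responder centre adds a(n1 − a)n0³/(n1·n0·N²) = 1 × 10 × 125/(55 × 256) = 0.0888. Variance: 4 × 0.0888/21.25² = 0.000786; SE = 0.0280. Lower bound +0.004.
- Sato: variance is (RD × ΣP + ΣQ)/21.25². With no placebo responders, P = [−n0²a + n1·n0(n0 − n1)/2]/N² and Q = a·n0/(2N). ΣP = 4 × (−25 − 165)/256 + 2 × (−120)/256 = −3.906; ΣQ = 4 × 5/32 = 0.625. Variance: (0.625 − 0.0588 × 3.906)/451.6 = 0.000875; SE = 0.0296. Lower bound +0.001.
- CMH: observed minus expected is 4 × 5/16 = 1.25; variance 4 × 55/256 = 0.859; z = 1.35, p = 0.18.

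Over random spreads of the four responders across centres, both lower bounds were above 0 in every simulated allocation.

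**False superiority rate (nominal 2.5%).** 400,000 simulated trials per point. Ranges cover three assumed splits of patients over centres.

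| Common response rate | Greenland-Robins | Sato |
|---|---|---|
| 1% | 0.3–0.4% | 0.3% |
| 2% | 2.2–2.5% | 2.1% |
| 3% | 4.9–5.3% | 4.8% |
| 5% | 8.1–8.3% | 7.9% |
| 6% | 8.0–8.3% | 7.9% |
| 10% | 6.1–6.4% | 5.6% |
| 20% | 5.1–5.2% | 4.0–4.1% |
| 30% | 4.5–4.6% | 3.5–3.6% |

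With near-equal centres the rate at 3% is 4.8 to 4.9%. The CMH test without continuity correction stays at or below 2.4% throughout. Exact enumeration of the unstratified Wald rule gives 7.9% at 5%, so the excess is not a product of the simulation.

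The shape has a simple cause. At 1%, only 64 × 0.01 = 0.6 active responders are expected, so the four needed are rarely reached. At 5%, 3.2 are expected and the placebo arm is empty about one time in five.

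**Power at 0.294 against 0.010, 64/32.** About 99.8% for the Wald-type rule, 99.1% for CMH and at least 98% for Fisher.

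**The case against.** The strongest objection is that the article names no interval formula. A score-type interval fits its wording, would not pass 4/64 against 0/32, and could be fixed in an analysis plan that is not shown. This stands, and it makes the finding conditional. It does not remove it. The article commits to an estimator, an interval, a threshold and an error rate, and the default interval for that estimator is built on its own variance. Both usual variances break the stated error.

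Four stronger readings are tempting but not supported:

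- *The rule is anticonservative at the placebo rate the plan expects.* It is not. At a common 1% the error is 0.3%, well under nominal. The excess begins just above 2%. But the 1% is a normal-model calculation from a 24-patient trial of six weeks, and the type I error has to hold at whatever common rate is true.
- *Sizing on Fisher and deciding by another rule is an error.* It is not in itself. The calculation reproduces, and power is ample under every rule considered.
- *4/64 against 0/32 is a likely result.* Under the planning rates about 19 active responders are expected (64 × 0.294 = 18.8). Four to seven with none on placebo has a chance of about 0.03%. The example shows where the boundary lies, not what the trial would probably observe.
- *The fitness-to-drive analysis has the same fault.* No error rate was computed for it. It tests against a margin of −32%, so nothing is claimed here.

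**Conclusion.** The concern holds in conditional form. If the corresponding interval is Wald-type with the Greenland-Robins or Sato variance, the primary rule does not hold 2.5% in the direction of superiority. The rate is about two to three times nominal at common response rates of 3 to 10%, with a peak of about 8% at 5 to 6%, and a milder excess persists to 30%. At 1 to 2% the rule is at or below nominal. If a score-type interval is intended, the 4/64 against 0/32 example fails to pass, as it should, and one sentence saying so settles the point.

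The figures rest on assumed centre sizes (three splits gave similar results), on equal true rates in the two arms and on complete enrolment at 64/32. The sample size and the stated power are not in question.

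**What to change.** In Primary Analysis, base the superiority decision on the centre-stratified CMH test, without continuity correction, at two-sided 5% with the difference favouring nabiximols. Report the Mantel-Haenszel risk difference with a stratified score-type (Miettinen-Nurminen) 95% interval, and state that the test decides. Fix both before unblinding.

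The cost is wording only: no change to patients, visits or data. Power at the planned rates falls from about 99.8% to about 99.1%, a loss of 0.7 percentage points, and stays well above the 90% target.

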#### Key Secondary Analysis

If the primary null hypothesis will be rejected and superiority of the active treatment over placebo will be demonstrated, non-inferiority of the active treatment compared to placebo will be hierarchically tested regarding the proportion of patients' fitness to drive at the 2-sided significance level of 5% in all patients. The analyses will be done with a Mantel-Haenszel estimate for the risk difference (active treatment minus placebo) stratified by center. If the lower bound of the corresponding 95%-confidence interval is above the non-inferiority margin of −32%, non-inferiority of the active treatment over placebo regarding fitness to drive will be concluded.

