### Active Treatment Phase

The titration phase will last 4 weeks in all patients, independently of the maximum dose and the time for up-titration. The starting dose will be 1 spray/day (= 100 μl spray = 2.7 mg THC/2.5 mg CBD). The standard dose escalation will be the following: For the first 4 days, dose can be increased by 1 spray every 2 days, and thereafter by 1 spray every day up to a maximum dose of 12 sprays/day (= 1,200 μl spray = 32.4 mg THC/30 mg CBD). However, depending on individual tolerability and efficacy slower dose increase is possible. Patients will be allowed to increase their dose to achieve sufficient efficacy in both, the active and the placebo - treatment group to reflect that due to high inter-individual variability different patients may require different doses. Since no target dose is defined, dosage can be increased until the patient reaches his/her individually tolerated maximum dose (1–12 sprays/day) based on the patient's judgment and investigator's assessments. Different dose levels thus reflect different needs of patients with different patient characteristics and not a systematic dose-response investigation. For patients in the placebo arm, titration will follow the same scheme as for nabiximols.

After the 4-weeks titration phase, treatment will be continued at a stable dosage for another 9 weeks. However, dose adjustment will be possible. Thereafter, medication will be withdrawn without down-titration.

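### Non-inferiority of fitness to drive is concluded from one all-patients analysis, so non-compliance on nabiximols and cannabis use on placebo favour the claim and no on-treatment set has to agree

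*Protocol article*

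**What the plan says.** The Key Secondary Analysis section opens with a gate: "If the primary null hypothesis will be rejected and superiority of the active treatment over placebo will be demonstrated", fitness to drive is tested next. It then fixes three things.

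- Population and level: "fitness to drive at the 2-sided significance level of 5% in all patients".
- Estimator: "The analyses will be done with a Mantel-Haenszel estimate for the risk difference (active treatment minus placebo) stratified by center".
- Decision rule: if the lower 95% bound lies "above the non-inferiority margin of −32%, non-inferiority of the active treatment over placebo regarding fitness to drive will be concluded".

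The article names no per-protocol, compliant or on-treatment set for this test.

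Four other places bear on the point.

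- Sample Size Calculation enlarges the trial: "To compensate for a potentially diminished treatment effect due to self-medication, non-compliance, and drop-out".
- Compliance plans THC testing to check both intake of study medication and concomitant cannabis use.
- Table 1 schedules compliance questions at every treatment visit and blood cannabinoids at visit 10, which is also the scheduled driving-test visit.
- Driving Test "Fitness to Drive" places the follow-up test at visit 10 or before study medication is discontinued.

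**The concern.** In the superiority test on tics, patients who do not take the drug, or who take cannabis on placebo, make the arms look alike and count against the claim. In a non-inferiority test the same process counts for it. The enlargement from 75 to 96 patients helps only the first test. In the second, more patients narrow the interval around a difference that is already shrunk.

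At stake is the only secondary claim in the testing hierarchy. The Discussion presents it as an important practical question for patients, and under the German rules described in the Introduction patients must judge their own driving ability. With a margin already 32 points wide, there is little room for a rule that dilution can help to satisfy.

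**Working it through.** **1. The plan's own figure.** Inputs from Sample Size Calculation: the calculation is "based on an exact Fisher-test with a two-sided significance level of 5"%, with "a power of 90%, and the above-mentioned responder rates (placebo = 0.010, THC = 0.294") and 2:1 allocation. Exact enumeration with 2.5% in the upper tail gives power of 89.9% at 48:24 and 91.7% at 50:25, so the stated 50 + 25 = 75 reproduces. The increase is 96/75 = 1.28, matching the stated increase of about 30%. This sizing is for tic response; the article gives none for the driving test.

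**2. How dilution enters.** Let p be the fitness rate on placebo and let the true on-drug loss be exactly at the margin, 0.32. Let f be the share of the active arm not taking drug at the test and performing like placebo. Then

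- active rate = p − 0.32(1 − f)
- expected difference = −0.32(1 − f)

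This gives −30.4 points at f = 5%, −28.8 at 10% and −26.6 at 17%. A share g of placebo patients using cannabis and impaired to the same degree gives placebo rate p − 0.32g and expected difference −0.32(1 − g), the same shrinkage.

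**3. Chance of a false claim.** This is the sum of the binomial probabilities of all outcomes (x fit of n on active, y fit of m on placebo) for which

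x/n − y/m − 1.96·SE > −0.32, with SE² = (x/n)(1 − x/n)/n + (y/m)(1 − y/m)/m.

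This is an unstratified Wald interval, used to approximate the planned centre-stratified one. The article gives neither p nor f for driving, so both are assumed: p from 60% to 90%, f as shown. Numbers tested run from 21:11 (about a third of 64:32, as two of six sites host the test) to all 64:32.

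| Dilution f | False non-inferiority |
|---|---|
| 0% | about 2–3% |
| 5% | 2.4–3.6% |
| 10% | 3.2–5.2% |
| 17% | about 5–9% |

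The nominal rate is 2.5%.

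Hand check at 64:32, p = 0.80, f = 10%: the active rate is 0.80 − 0.288 = 0.512, and SE = √(0.512 × 0.488/64 + 0.80 × 0.20/32) = 0.094. The normal approximation is Φ(0.032/0.094 − 1.96) = Φ(−1.62) ≈ 5.3%, against 4.3% by exact enumeration. Undiluted, the corresponding figures are 2.5% and 2.0%. Both roughly double.

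**4. Drop-out, taken separately.** A patient tested before stopping is still on drug and does not dilute. A patient who misses the test has no value, and the effect depends on the missing-data rule. As an illustration, count missing as unfit, with the on-drug loss at 32 points:

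- Equal 17% missing: −0.32 × 0.83 = −26.6 points, towards the claim.
- The earlier trial's split, 3 THC and 1 placebo, of 12 per arm: at p = 0.60, 0.28 × 0.75 − 0.60 × 0.917 = −34 points; at p = 0.80, 0.48 × 0.75 − 0.80 × 0.917 = −37 points. Both go against the claim.

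The direction for drop-out is therefore open.

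**The case against.** **Analysis sets belong to the statistical analysis plan, which is not shown.** This is true in general, and the mere absence of a per-protocol set would be no finding. Here, however, the article prints a complete rule under which one interval is enough. A supportive analysis added later could disagree and the claim would still stand.

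**The phrase about all patients may only contrast the whole trial with the two driving-test sites.** That is a fair reading, and the documents do not establish that an intention-to-treat set is meant. Under either reading, no compliant set has to agree.

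**Superiority on tics must come first.** This is a partial safeguard. It makes a largely unexposed active arm unlikely, but does not show that the driving comparison is undiluted.

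**An on-treatment set departs from randomisation and may lose patients who stopped for intolerance.** This would be serious if that set replaced the all-patients analysis. Requiring success in both sets cannot make a false claim more likely than the printed rule does.

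**Tempting stronger readings.** A reader might take the earlier trial's drop-out (17% overall, 3 of 12 on THC) or the 30% sample-size increase as the share off drug at the driving test. The documents do not support this: the test is planned before discontinuation, and the 30% is an allowance for three causes together, made for the tic endpoint. Nor is the individual titration dilution; it is the planned treatment. Cannabis use in the nabiximols arm, which Limitations calls unlikely, would not dilute exposure and could act against the claim.

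**Conclusion.** The point holds in a limited form. The printed rule lets a single all-patients interval establish non-inferiority, and two processes that the article anticipates, non-compliance on nabiximols and cannabis use on placebo, push that interval towards the claim. The direction is firm for these two and unsettled for drop-out.

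The size is moderate and depends on assumptions. At 5–10% dilution the false-claim rate is 2.4–5.2%, up to about twice nominal; at 17% it is about 5–9%. The 17% row is a sensitivity value, not a forecast. All rates assume a true loss exactly at the margin, an unstratified Wald interval and placebo fitness of 60–90%.

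A reader might infer that the trial is likely to clear nabiximols for driving wrongly, or that the rule is anti-conservative in every respect. The documents support neither. The weakness is a decision rule with no check against dilution, and it should be corrected.

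**What to change.** Amend the Key Secondary Analysis so that non-inferiority is concluded only if the lower 95% bound exceeds the margin in both of two sets:

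1. all patients with a follow-up driving test;
2. an on-treatment set whose definition is fixed before unblinding.

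The second set should keep patients tested just before discontinuation. It should exclude only those not taking study drug at the test and, on placebo, those positive for THC. The compliance questions and blood cannabinoid samples already planned supply the data. THC blood results are held confidentially by an outside laboratory, which can apply the THC criterion without unblinding the trial team. Because driving visits may vary for patients from other sites, the definition should say which sample is matched to the test. The analysis plan should also state how missing driving tests are treated, since that decides which way drop-out acts.

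The cost is a change of wording, one further run of the same Mantel-Haenszel analysis, and slightly lower power for the non-inferiority claim because both sets must succeed. No new assessments are needed.

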#### Secondary and Safety Analyses

As secondary analysis, we will use YGTSS-TTS change from baseline at 9 weeks of treatment as continuous outcome variable. An ANCOVA will be computed with the covariates: baseline YGTSS-TTS and center. Additionally, a mixed model will be carried out to assess longitudinal changes in YGTSS-TTS (measured by YGTSS-TTS change from baseline to week 4 and week 9). The model will include repeated measures with a first-order autoregressive covariance structure, and include baseline YGTSS-TTS and center as covariates. For this model, the missing values will not be replaced. Further secondary endpoints will be analyzed with the same statistical methods. All secondary analyses are exploratory. Further exploratory analyses may investigate, whether the finally required dose can be related to baseline patient characteristics so that dose recommendations could be given to the patients.

Absolute and relative frequencies of (S)AEs will be calculated for the full analysis set and will be compared between treatment groups by using a chi-squared test.

